#### Economic evaluation

The economic evaluation will employ a within-trial design whereby the individual-level costs and outcomes of the randomised student participants will be analysed. A modelled economic evaluation will also be undertaken using the results of this trial and relevant epidemiological literature to extrapolate long-term costs and consequences that are not fully captured within the trial. The economic evaluation will comprise both a cost-utility analysis and a cost-consequences analysis. The cost-utility analysis will evaluate the cost-effectiveness of the intervention in terms of the cost per QALY, where costs are estimated using the RUQ and QALYs are measured using the CHU9D. A cost-consequences analysis will also be conducted to compare the incremental costs of the intervention to the full spectrum of outcomes included in the study (i.e. change in suicidal ideation, depressive symptoms, hopelessness, and problem-solving capability). This will produce a set of alternative cost-effectiveness ratios, an approach that has been deemed useful by decision-makers. The economic evaluation will be primarily conducted using the health sector perspective. A broader societal perspective will also be undertaken in a secondary analysis. The evaluation will first measure and value any change to the use of health care resources over the period of the study between the two arms of the trial (intervention and control) and then compare any additional costs to other outcomes achieved.

Standardised economic evaluation techniques including incremental analysis of mean differences and bootstrapping to determine confidence intervals will be employed. If the intervention is found to be effective, the lifetime and population budgetary impacts and cost-effectiveness of the intervention will be determined using modelling techniques.

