### Procedure

Participants will be assessed at four time-points: baseline (T1), 2 weeks post-baseline (T2), 12 weeks post-baseline (T3), and 24 weeks post-baseline (T4). The T2 assessment will be completed immediately following participation in the safeTALK workshops, and T3 at the end of the Reframe IT intervention period (see Table 1).

**Table 1 Tab1:** Schedule of assessments and interventions

Time point		Study period				
	− T1	T1	T2		T3	T4
		Baseline Week 1	Week 3	Weeks 4–12	Week 12	Week 24

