**Assessments:**						
Demographics		X				
Purpose-designed 3-item questionnaire assessing exposure to suicide and suicide prevention training		X				
Suicidal Ideation Attributes Scale (SIDAS)		X	X		X	X
Single item measuring current suicidal ideation		X	X		X	X
Youth Risk Behaviour Survey (YRBS)—suicide items		X	X		X	X
Patient Health Questionnaire-9 (PHQ-9)		X	X		X	X
Distress Questionnaire-5 (DQ-5)		X				
Hopelessness Scale for Children (HSC)		X	X		X	X
Negative Problem Orientation Questionnaire (NPOQ)		X	X		X	X
Resource Use Questionnaire (RUQ), adapted from the Young Mind Matters Service Use questionnaire (BRIEF VERSION)		X				
Resource Use Questionnaire (RUQ), adapted from the Young Mind Matters Service Use questionnaire (FULL VERSION)			X		X	X
Purpose-designed questionnaire asking about previous help-seeking behaviour and future help-seeking intentions from family, friends and other “informal” sources of help		X	X		X	X
4-item measure of attitudes towards help-seeking from adults at school, derived from the previous US Sources of Strength (SOS) trial and currently being used in the Australian SOS trials		X	X		X	X
4-item measure assessing attitudes towards overcoming secrecy barriers, derived from the previous US Sources of Strength (SOS) trial and currently being used in the Australian SOS trials		X	X		X	X
Willingness to Intervene Against Suicide Questionnaire (WIS)		X	X		X	X
Stigma of Suicide Scale (SOSS)—short form		X	X		X	X
Literacy of Suicide Scale (LOSS)—short form		X	X		X	X
Child Health Utilities Index 9 Dimension (CHU9D)		X	X		X	X
Purpose-designed 7-item questionnaire assessing acceptability of safeTALK training			X			
Purpose-designed 11-item questionnaire assessing acceptability of the Reframe IT intervention (or of not receiving it)					X	
Two items from the Patient Health Questionnaire-4 (PHQ-4), measuring anxiety		X				
Purpose-designed 11-item scale measuring experimentally induced distress, adapted from Yeater, Miller, Rinehart and Nason (2012)						X

***Note. Informed consent for Reframe IT participation and evaluation will be collected from eligible participants between Times 1 and 2, prior to randomisation and commencement of the Reframe IT intervention

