Change in suicide literacy at T2, T3, and T4 when compared to T1 will be assessed using the Literacy of Suicide Scale (LOSS)—Short Form [55]. This scale contains 12 items rated on a “true/false/don’t know” scale. The correct response for items 1, 3, 4, 5, 7, 8, and 10 is “false” while items 2, 6, 9, 11, and 12 are correctly answered “true”. The scale provides a total literacy score (percent correct) where higher scores indicate greater suicide literacy.

Change in health-related quality of life during the course of the trial (T1, T2, T3, and T4) will be assessed using the Child Health Utility—9 Dimension (CHU9D) [56]. The CHU9D is a multi-attribute utility instrument suitable for young people aged 7–17 years. It comprises a short questionnaire alongside a set of preference weights using general population values. The questionnaire has nine items with five response levels per item and can be used to derive quality-adjusted life years (QALYs) for use in a cost-utility analysis (i.e. the economic evaluation).

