### Randomisation and treatment allocation

Students who consent to participate in Component 2 will be randomised to the intervention group (Reframe IT plus TAU) or to the control group (TAU only) using block randomisation with varying block sizes and stratified by school. The allocation ratio will be 1:1. The randomisation schedule is computer generated by independent Information Technology (IT) personnel with guidance from the study statistician. The schedule will then be implemented by a member of the study team (other than the statistician) into the REDCap database management software for allocating treatments to individual students.

A member of the study team will inform school wellbeing staff of the outcome of randomisation, and they will then inform students. With the exception of the study statistician, study team members are not blind to the treatment allocations. The study statistician will not have access to the randomisation component of the database and will not be told about the treatment allocations, and will therefore remain blinded. As the study statistician will not be involved in any aspect of this study operations other than data analysis, there are no circumstances we could foresee under which the study statistician would be required to be unblinded.

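### The economic evaluation names bootstrapped mean differences and states no adjustment of incremental QALYs for T1 CHU9D, which, taken as written, gives up precision and leaves part of any chance T1 imbalance in the result

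*Protocol article*

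**What the plan says.** The Economic evaluation section of the protocol article describes a within-trial cost-utility analysis of the randomised students, in which "costs are estimated using the RUQ and QALYs are measured using the CHU9D". Its statement of method is: "Standardised economic evaluation techniques including incremental analysis of mean differences and bootstrapping to determine confidence intervals will be employed". The section mentions no covariate, regression model or baseline utility.

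Under Secondary outcomes the utility measure is scheduled at every visit: "Change in health-related quality of life during the course of the trial (T1, T2, T3, and T4) will be assessed" with the CHU9D. The Procedure section places the visits at weeks 0, 2, 12 and 24. The note to Table 1 says that consent for Reframe IT is collected "between Times 1 and 2, prior to randomisation and commencement of the Reframe IT intervention", so the T1 value is a true pre-randomisation measurement.

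The Randomisation section allocates students "using block randomisation with varying block sizes and stratified by school", and "The allocation ratio will be 1:1". Under Statistical analyses, Component 2, arm characteristics are compared descriptively to look for imbalance. The primary outcome is analysed as a difference in change by mixed model with school as a random factor, and secondary outcomes are to be handled in a similar way. That section does not say that its model also governs the QALY comparison.

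**The concern.** A QALY is a level accumulated over follow-up, not a change from a starting point. A student who begins with higher utility tends to accumulate more QALYs whatever the allocated arm, partly because the T1 value enters the total and mainly because later values correlate with it. If the arms differ by chance at T1, an unadjusted difference in mean QALYs carries some of that difference. Bootstrapping the unadjusted difference expresses its uncertainty but does not remove the imbalance that occurred or recover the lost precision.

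The follow-up is 24 weeks, so a full unit of utility sustained throughout is worth only 24/52 = 0.46 QALY, and a realistic difference between arms will be a small fraction of that. Cost-effectiveness is a declared secondary aim, and the trial results are to feed a longer-term economic model, so avoidable noise in the within-trial QALY difference would be carried forward. If the method is not fixed in advance, adjustment also remains open to choice after the imbalance has been seen.

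**Working it through.** **Plan's own figures.** The protocol gives no QALY figure to reproduce. The only stated figure used here is 134 per arm. It is obtained from 2 × (42.3 × (1.960 + 0.842) / 14.5)² = 133.6, rounded up to 134, without the stated design effect of 1.1. With the design effect the result would be 147. That is a separate matter and does not affect this point.

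**Inputs from the document.** Visits at weeks 0, 2, 12 and 24 (Procedure); 134 per arm (Sample size and power calculation).

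**Assumptions.** CHU9D utility SD 0.15 to 0.25, the same at each visit; correlation ρ between any two visits 0.3 to 0.7; QALYs by the trapezoid rule from week 0; complete data; no allowance for school.

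**Trapezoid weights (years).**
- T1: 1/52 = 0.019 (4.2% of the 24 weeks)
- T2: 6/52 = 0.115 (25%)
- T3: 11/52 = 0.212 (45.8%)
- T4: 6/52 = 0.115 (25%)
- Sum: 24/52 = 0.4615

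**Formulas.**
- Slope of QALY on T1 utility: b = 1/52 + ρ × 23/52.
- Share of a fully sustained imbalance that reaches the QALY difference: b / 0.4615.
- QALY variance: SD² × [(1 − ρ) × Σw² + ρ × (Σw)²], with Σw² = 194/2704 = 0.0717 and (Σw)² = 576/2704 = 0.2130.
- r² = b² × SD² / QALY variance. The adjusted SE is the unadjusted SE × √(1 − r²).

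| ρ | b | share passed on | r² | SE reduction from adjusting |
|---|---|---|---|---|
| 0.3 | 0.152 | 33% | 0.20 | 11% |
| 0.5 | 0.240 | 52% | 0.41 | 23% |
| 0.7 | 0.329 | 71% | 0.63 | 39% |

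**In QALYs, 134 per arm.** The SE of the T1 imbalance is SD × √(2/134). Multiplying by b gives the shift from a one-SE imbalance.

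| SD | ρ | SE of T1 imbalance | shift | unadjusted SE | adjusted SE |
|---|---|---|---|---|---|
| 0.15 | 0.3 | 0.0183 | 0.0028 | 0.0062 | 0.0055 |
| 0.20 | 0.5 | 0.0244 | 0.0059 | 0.0092 | 0.0071 |
| 0.25 | 0.7 | 0.0305 | 0.0100 | 0.0126 | 0.0076 |

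The shift divided by the unadjusted SE equals r, so a one-SE imbalance moves the estimate by about 0.45 to 0.80 of its own standard error (√0.20 to √0.63).

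**Sensitivity to sample size.** If all 335 randomised students contributed, about 167 per arm, shifts and standard errors would be about 10% smaller (√(134/167) = 0.90). The percentage reduction from adjusting would not change.

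**The case against.** The strongest reply is that the sentence commits to nothing wrong. A reader might infer that the protocol plans an unadjusted comparison. It does not say so: the list of techniques is explicitly non-exhaustive, and a regression-adjusted incremental QALY is also a mean difference that can be bootstrapped. A journal article also commonly leaves covariates to an analysis plan, and none is shown here. CHU9D is listed among the secondary outcomes in terms of change, and those outcomes are to be analysed much like the primary one. All of this stands, and it limits the point to a request to state the adjustment. What remains is that the economic section names its own estimator with no covariate, and nothing extends the change model to QALYs.

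A reader might also infer that a T1 imbalance passes in full into the cost per QALY. It does not. T1 carries only 4.2% of the QALY weight directly; the rest of the effect depends on correlation with later visits.

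Nor is bias shown. With 1:1 allocation the unadjusted difference is unbiased over randomisations, and its bootstrap interval already reflects the variability due to chance imbalance.

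Finally, the size rests on assumed values, and at a correlation of 0.3 the gain in precision is modest. That also stands.

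**Conclusion.** The point holds as a worthwhile improvement to a secondary analysis, not as an error that invalidates it. The stated method includes no adjustment for a utility value measured before randomisation, and the design does not balance that value. Taken as written, the cost is conditional chance error and lost precision. The shift is about 0.003 to 0.010 QALY for a one-standard-error T1 imbalance, of which the arithmetic passes on about 33% to 71% relative to an imbalance sustained for the full 24 weeks. Adjustment would make the standard error about 11% to 39% smaller. These figures rest on the assumed SD and correlation, the trapezoid calculation and 134 per arm, and apply only if the analysis is in fact unadjusted. The documents do not support saying that an unadjusted analysis is prescribed, that the imbalance is transferred whole, or that the estimate is biased.

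**What to change.** Add to the Economic evaluation section, or to the economic analysis plan before any comparison by arm, that incremental QALYs are estimated by regression on treatment arm with T1 CHU9D utility as a covariate and school in the model. State that the bootstrap is applied to that adjusted model, with each student's cost and QALY resampled together so that their correlation is kept.

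The cost is a sentence or two of text. The T1 CHU9D is already collected, so no visit, instrument or sample size changes. Reporting net benefit or an acceptability curve alongside the ratio is an optional presentation choice and not part of this request.

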### Safety, supervision, and committees

The organisational structure of this trial is as follows. The MAPSS steering committee is comprised of the CI, project manager, and clinical supervisor and is responsible for investigator oversight of the MAPSS project. The MAPSS steering committee meet on a fortnightly basis. The MAPSS Safety Monitoring Committee (SMC—Equivalent to the Data Safety and Management Committee (DSMC)) is the main vehicle for safety management, data monitoring, endpoint adjudication, and data management strategy. This committee is comprised of the CI, project manager, as well as independent internal and external subject matter experts including the Sponsor. The composition of the group was designed to incorporate transparency and so that no one set of competing interests could unduly influence other stakeholders, and is appropriate for this non-commercially funded or sponsored study. This committee has a dual safety role: it incorporates a risk-appropriate safety, endpoint adjudication, and data management strategy which is responsive to study issues as they eventuate. The committee meets on a quarterly basis and on an ad hoc basis when deemed necessary by the steering committee. The charter for this committee is outlined in the SMC manual, available upon reasonable request by contacting the corresponding author.

A comprehensive safety protocol has been developed, which will be activated if: (1) participants return a score of 1 or higher on the SIDAS at any time-point (the established cut-off [45] indicating any level of suicidal ideation in the past month); (2) participants report current suicidal ideation at any time-point; (3) participants report suicide risk via the Reframe IT platform. Where possible, the school will be responsible for checking in with the participant and managing any risk, although in some cases researchers will assist with this (e.g. where the school does not have the capacity to follow up with students in a timely way). If this is required, the researcher will contact the participant by phone and conduct a brief risk assessment. The response will depend on the level of risk, and ranges from providing the participant with contact information for helplines (in the case of low risk) to calling the participant’s emergency contact or emergency services (in the case of high-severe risk). All participants will be required to provide emergency contact information via the consent form. Ultimately, all risk information will be communicated to the school, who will be responsible for ongoing management. There are no planned interim analyses for this study, nor are there any stopping guidelines other than as outlined in section “Study discontinuation criteria” of this protocol.

Supervision will be provided to the researchers from the study clinical psychologist, who will also be on call during each assessment session.

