#### Screening for risk

The screening will take the form of self-report measures embedded into the questionnaires at each time point. Students who report suicidal ideation within the past 4 weeks (SIDAS score of 1 or higher) or any level of current suicidal ideation (single multiple-choice item) will be contacted by a member of the school wellbeing team or the research team, who will assess risk and refer them to appropriate support.

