### Outcomes and measures

#### Primary outcome

The primary outcome for this study is change in past 4-week suicidal ideation at T3 and T4 when compared to T2, assessed via the SIDAS [45]. The SIDAS is designed to screen individuals in the community for presence of suicidal thoughts and assess the severity of these thoughts. It comprises five items, each targeting an attribute of suicidal thoughts: frequency, controllability, closeness to attempt, level of distress associated with the thoughts and impact on daily functioning. Responses are measured on a 10-point scale. Total SIDAS scores are calculated as the sum of the five items, with controllability reverse scored (10 = 0, 9 = 1,…, 0 = 10), with total scale scores ranging from 0 to 50. Items are coded so that a higher total score reflects more severe suicidal thoughts.

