#### Additional measures

To characterise the sample at baseline, participants will be administered a standard demographic questionnaire. They will also be asked about any previous mental health diagnoses, exposure to suicide in others, and any previous suicide prevention training undertaken.

At each time point, participants will be asked about their history of suicide planning and attempt, using the four suicide items from the Youth Risk Behaviour Survey (YRBS) [57]. These yes/no items assess if the respondent has had suicidal ideation or made a suicide plan or attempt (and its seriousness) during the past 12 months at baseline, or in the period between assessment points.

Participant views on the safeTALK workshop, including whether or not they thought it was “enjoyable”, “upsetting”, and “worthwhile”, will be assessed at T2 only using seven purpose-designed items. Participant views on the Reframe IT intervention (or for those in the control group, acceptability of *not* receiving Reframe IT) will be assessed using 11 purpose-designed items at T3 only.

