Based on pilot data, and in consideration of the self-reported nature of the data collected, we estimate that, to recruit the required 268 students, we need to screen 4020 students (see Fig. 1). This is based on 20% drop-out rate among those who are classed as high-risk, consenting, and randomised; 33% of those identified as high-risk consenting to participate in the trial and being randomised (335 consenting and randomised, and analysed on an intention-to-treat basis); and 25% of the total sample endorsing suicidal ideation within the past month (1005 students). There are 141 mainstream secondary schools in the region and approximately 140 year 10 students per school. It is therefore estimated that approximately 29 schools will be recruited in total, although this number may fluctuate depending on the rate of student recruitment. Schools will be recruited in batches throughout the project. If the target sample size is reached before the 29 schools have been recruited, no further schools will be recruited. Similarly, if we recruit the target 29 schools but fail to recruit the required number of participants, more schools will be invited to participate. In the event that we struggle to meet the recruitment target, or if it is unfeasible to recruit year 10 students at a particular school, year 11 students may also be recruited.

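### A suicide plan or attempt reported on the YRBS items triggers no safety contact, so an attempt more than 4 weeks old at T3 or T4 can meet none of the listed triggers

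*Protocol article*

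**What the plan says.** All references are to the protocol article.

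- **Safety, supervision, and committees** gives a numbered list of conditions for the safety protocol, "which will be activated if: (1) participants return a score of 1 or higher on the SIDAS at any time-point". The second condition reads "2) participants report current suicidal ideation at any time-point" and the third "3) participants report suicide risk via the Reframe IT platform".
- **Screening for risk** uses the two questionnaire conditions as its rule for who is contacted, assessed for risk and referred: "Students who report suicidal ideation within the past 4 weeks (SIDAS score of 1 or higher) or any level of current suicidal ideation".
- **Procedure** describes one automatic REDCap flag, for SIDAS scores of 1 to 20. The manual check of paper questionnaires is also of the SIDAS alone.
- **Additional measures** has four YRBS suicide items asked at every time point. They cover whether the student has had ideation or has "made a suicide plan or attempt (and its seriousness) during the past 12 months at baseline, or in the period between assessment points". The schedule in Table 1 confirms T1 to T4.
- **Primary outcome** gives the SIDAS recall: "change in past 4-week suicidal ideation at T3 and T4 when compared to T2, assessed via the SIDAS". The current-ideation item under Secondary outcomes asks only about the present moment.

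No section makes a positive YRBS plan or attempt answer a reason to contact the student.

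**The concern.** The study asks every student about recent attempts and their seriousness, but its stated contact rule does not use the answer. A SIDAS score of 1 on a 0 to 50 scale prompts contact; a reported attempt, taken alone, does not. The article's own Background says that non-fatal attempts are associated with later suicidal behaviour and suicide.

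At stake is participant safety; the trial's inference is unaffected. Randomised students had a SIDAS of 1 or more at T1 by the Component 2 entry criterion, so the safety system already knows them. Most Component 1 students are not expected to have triggered it at T1, and for them a YRBS answer at T3 or T4 could be the first signal.

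Recording of adverse events is not in dispute: it is unconditional under Assessment and documentation of AEs. The point concerns only the rule for contact and risk assessment.

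**Working it through.** The plan states no figure to reproduce. The check compares what each trigger can see with what the YRBS items ask.

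**Inputs**

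- Assessment times, from Procedure: T1 at week 0, then "2 weeks post-baseline (T2), 12 weeks post-baseline (T3), and 24 weeks post-baseline (T4").
- SIDAS recall: 4 weeks. Current-ideation item: the present only.
- YRBS recall: 12 months at T1, then the interval since the previous assessment.
- Screening projection, from Sample size and power calculation: 4020 students screened, with "25% of the total sample endorsing suicidal ideation within the past month (1005 students").

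**Time the SIDAS does not cover**

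Uncovered weeks = max(0, interval − 4).

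| Assessment | Interval (weeks) | Uncovered (weeks) |
|---|---|---|
| T2 | 2 − 0 = 2 | max(0, 2 − 4) = 0 |
| T3 | 12 − 2 = 10 | 10 − 4 = 6 |
| T4 | 24 − 12 = 12 | 12 − 4 = 8 |

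The total is 0 + 6 + 8 = 14 weeks. Over the 24 weeks after baseline this is 14/24 = 58%; over the 22 weeks from T2 to T4 it is 14/22 = 64%. Table 1 labels T2 as week 3 and T3 as week 12, which would make the T3 interval 9 weeks and its uncovered part 5. The conclusion does not depend on which is used.

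**Tracing one student through the list**

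Take a student who at T3 or T4 reports an attempt six weeks earlier, scores 0 on the SIDAS and denies current ideation. A SIDAS of 0 is possible, since the stated range starts there.

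1. SIDAS of 1 or more: not met, because the attempt lies outside the recall period and no ideation is reported within it.
2. Current ideation: not met.
3. Risk reported on the Reframe IT platform: open only to students using Reframe IT, so not to controls or to students outside Component 2. For users it requires a separate report and does not act on the YRBS answer.

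The Screening for risk rule contains only the first two conditions, so it gives the same result.

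**Students with no SIDAS trigger at T1**

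4020 − 1005 = 3015, and 3015/4020 = 75%. This is the projected group with no past-month ideation at baseline. It is not the number who fall in the gap.

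**The case against.** **The full safety protocol is not shown.** The article condenses a longer document that may hold further triggers. This stands as a limit on what can be concluded about practice. But the article states the activation conditions as a numbered list and repeats the questionnaire conditions under Screening for risk, and the flag and paper check under Procedure also rest on the SIDAS. The published rule is therefore consistent in leaving the YRBS answers out. If the full document differs, the article needs aligning with it.

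**Adverse event handling offers another route.** An attempt since the last assessment would normally count as an adverse event, causality must be assessed, and information is sought from the participant where possible. That could bring the student to the team's notice. However, the section does not name the YRBS items as a source and does not require a risk check. It also depends on someone having noticed the answer, which is what a trigger would secure.

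**The scenario is narrow.** The existing thresholds are already very low, every student is screened again at T2, T3 and T4, and a clinical psychologist is on call at each session. The student must report an older attempt, score exactly 0 and deny current ideation. This is accepted. It limits how often the gap matters, but does not justify collecting an attempt report with no stated response.

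**Where to cut off past behaviour is a judgement.** At T1 the YRBS looks back 12 months, so the uncovered time there is longer, about 52 − 4 = 48 weeks. That is fair: the point made here is confined to events arising during the study, which makes it narrower than it could be.

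**Conclusion.** The concern holds. As published, the contact and risk-assessment rule omits the YRBS plan and attempt answers. An attempt more than 4 weeks old, reported at T3 or T4 with a SIDAS of 0 and no current ideation, meets no questionnaire trigger. The third trigger helps only a Reframe IT user who also reports risk there.

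The percentages above are shares of recall time and should not be read as a miss rate. How many students would be affected cannot be derived from the article.

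The conclusion assumes that the published list is the rule staff will follow. The matter should be fixed because the answer is already collected, the possible consequence is serious and the remedy is cheap. Sample size, randomisation and analysis are untouched.

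**What to change.** 1. Add a fourth condition to the list under Safety, supervision, and committees: a positive YRBS suicide plan or attempt answer at T2, T3 or T4 for the period since the last assessment. Add the same condition to Screening for risk.
2. Set a REDCap flag for it and include it in the manual check of paper questionnaires.
3. Keep the response graded by level of risk, as the safety section already provides.
4. Pass attempts found this way into the existing AE and SAE recording and causality assessment.
5. If the full safety protocol already contains this trigger, amend the published list to match.

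The cost is one database flag, one line in the paper-form check and one clause in each of two sections. The downside is a modest number of extra check-ins for school wellbeing staff or researchers, and some extra event assessments. Restricting the trigger to plan and attempt answers since the last assessment keeps that load down. The team may also wish to decide, and state, whether a plan or attempt in the 12 months before T1 should prompt contact.
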